#### Questionnaires

Several questionnaires were used to collect data using specifically designed software. All results were subsequently uploaded to a central database using the WiPam application [32].

*Background characteristics* included variables such as sex, age and socio-demographic status.

Socioeconomic status was mapped as suggested by W. C. Cockerham [33]. A total score was calculated as the sum of marital status (single, divorced, widowed (0) or married (1)), education (primary school or none (1), unfinished secondary education (2), secondary education (3), secondary vocational education (4), unfinished higher education (5) or higher education (6)), income (insufficient nutrition (1), minimally sufficient for food/clothing (2), sufficient to purchase TV/refrigerator but not a car or housing (3) or can purchase expensive goods (car/housing) (4)), and occupation (agricultural/unskilled worker (1), skilled worker (2), office clerk without higher education (3), manager/professional (4) or top manager (5)) [33].

#### Smoking anamnesis

Smoking status was specified as never smoker, former smoker (quit smoking 6 month ago or longer), or current smoker. Former and current smokers were asked about the age at which they began to smoke, how many years they had smoked and how many cigarettes per day they had smoked (in pack-years). One pack-year of smoking indicates that an individual smoked one package of cigarettes (20 cigarettes) daily for one year.

*Passive smoking status* was defined as both current smoking behavior using an environmental tobacco smoke (ETS) questionnaire [34] and lifetime ETS exposure [35]. The ETS questionnaire includes questions about short-term tobacco exposure (the past 7 days) in the household (living with smokers) or at other tobacco-polluted indoor or outdoor locations (e.g., any home, workplace, bar, nightclub, sport arena or concert hall). The lifetime ETS exposure questionnaire accounts for the long-term effects of tobacco exposure (the smoking status of the mother during pregnancy, the number of years in total that the subject lived with smokers, and how many years the subject was exposed to tobacco at the workplace). Environmental hazards (the number of years that the subject had lived in a polluted area) were also considered.

#### Occupational exposure

Occupational hazards (working in a dusty/toxic job) and indoor exposure to biomass fuels were assessed using additional questionnaires [36, 37]. The ATS 1978 Adult Questionnaire (ATS-DLD-78) was used to assess exposure to occupational hazards [36]. The participants were asked about working for one year or more in any dusty job, exposure to gas or chemical fumes, and the use of protective equipment. Limitations in work based on health problems or retirement were considered.

#### Exposure to indoor biofuel pollution

The participants were asked about personal gas or wood/stove use to estimate indoor exposure to biomass fuels [37]. Gas stove utilization ratings included none, low use (1–6 times/week) or high use (>7 times/week). Similar ratings were used for wood stove utilization: none, low use (1–4 times/week) or high use (>5 times/week).

#### Patient-reported family history and comorbidities

Information regarding family history of obstructive airway disease (asthma, chronic bronchitis, emphysema, chronic cough, and allergic rhinitis), personal history, including tuberculosis anamnesis, and co-morbidities (diabetes mellitus, myocardial infarction, arterial hypertension, arthritis, and allergic diseases) was collected in a systematic manner (yes or no). Additionally, the investigators recorded details regarding the use of current medications.

#### Respiratory symptoms

The participants were questioned about three primary symptoms (chronic cough, chronic sputum and a chronic dyspnea) [38]. The presence of chronic cough and chronic sputum production (defined as lasting more than 3 months) and chronic dyspnea were categorized as a chronic respiratory symptom.

#### Differential diagnosis between asthma and COPD

The International Primary Care Respiratory Group questionnaire was used to differentiate between asthma and COPD before spirometry [39, 40]. This questionnaire included questions regarding age, smoking history, respiratory symptoms, history of hospitalizations and treatment. The scoring system of this questionnaire utilizes a sum of the total number of points based on the patient’s responses: a score of 18 or less indicates a diagnosis of asthma, whereas a score of 19 or more suggests a diagnosis of COPD.

#### Spirometry

All participating investigators were invited to participate in a distance-learning course on spirometry, SpiroCourse [41, 42]. SpiroCourse was created and implemented by the RESPECT research team and was designed as a three-week E-learning course based on active learning principles. This course includes three tutorial modules (with assignments and quizzes), a library containing the most recently updated relevant guidelines, clinical cases and a discussion forum. The first module involves the fundamentals and procedures of spirometry. The second module focuses on acceptability and reproducibility quality criteria and reversibility testing. The third module focuses on comprehensive analyses, interpretation of the flow-volume curve and numerical data and quality control procedures. Practical training sessions (face-to-face), during which each participating investigator was required to demonstrate the skills required for this study, were organized in St. Petersburg and Arkhangelsk. All investigators completed the course successfully and agreed to receive continuous quality feedback on the exams.

#### Equipment

All centers were equipped with a portable turbine microspirometer (MIR Spirobank, Rome, Italy) and a personal computer equipped with the WiPam program to facilitate the upload of data to a central database. The Spirobank device is a hand-held instrument for lung function tests that can be connected to a computer. The accuracy of spirometry performed by the trained investigators using this equipment was previously examined in detail and is well documented [18]. The Spirobank spirometer performed very well in a laboratory environment compared with the Jaeger MasterScope, displaying a 2–5 % underestimation of the FEV_1_ and the FEV_1_/FVC. Moreover, we demonstrated that only 2 % of the observed variation in the measurement results could be explained by the type of device used under real-life conditions and that other sources of variation, such as the timing of the test, are more important than the small measurement error caused by the device itself.

Winspiro Pro software (MIR) was used to compare the measured values with those in reference tables and to automatically calculate the reproducibility of the performed spirometry in accordance with the ERS guidelines. The predictive values were calculated using Global Lung Initiative (GLI2012) Data Conversion software [22]. Two cut-offs values were used to define AL: FEV_1_/FVC < 0.7 (fixed cut-off) and FEV_1_/FVC < LLN (5^th^ percentile of z-scores of the GLI 2012 reference values).

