### Study I (prevalence and diagnosis)

#### Sample size calculations

The sample size was calculated based on two goals: 1) to determine a reliable estimate of the prevalence of COPD and 2) to estimate the diagnostic value of symptoms with an acceptable confidence interval.

To generate a reliable estimate of the prevalence of COPD, for which 8 % prevalence in the RF was assumed, the following formula was used: $$ n=\frac{Z^2P\left(1-P\right)}{d^2} $$, where n is the sample size, Z is the Z statistic for a level of confidence (95 %), P is the expected prevalence (8 %), and d is the desired precision (1 %) [31]. Therefore, based on our prevalence considerations, the sample size for the RESPECT study was estimated using 2828 subjects.

To estimate the diagnostic value of various signs and symptoms with an acceptable confidence interval (the second focus of our cross-sectional study), sample size considerations were based on the following premises: 1) the expected prevalence of important symptoms (i.e., chronic cough, dyspnea, wheezing, chronic phlegm) of COPD in the general population was 10 %; 2) a worst-case scenario that none of these criteria displayed any diagnostic value (i.e., the proportion of each symptom would be 0.5 in each group) given an acceptable confidence interval of 95 %; and 3) based on an 8 % prevalence of COPD. Based on these premises, a sample size of 864 was established.

Based on both of these approaches and assuming an anticipated refusal rate of 20 %, 3500 participants from St. Petersburg and 1500 from Arkhangelsk were invited to participate in this study.

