#### Procedure

The pre- and post-bronchodilator spirometry test measurements were recorded. Reversibility testing using 400 μg of salbutamol or 160 μg of ipratropium bromide (for patients older than 60 years or with comorbid cardiovascular disease) was offered to all participants. The second spirometry test was performed 15 (salbutamol) or 45 min (ipratropium bromide) after the first spirometry test. The Spirobank G turbine-microspirometer does not require calibration and has an internal temperature sensor for automatic BTPS conversion [43]. Routine multiple-speed volume calibration checks are not mandatory with this equipment. Nevertheless an extra calibration procedure was organized twice during the research using a 3 liter calibration syringe and no significant deviations were detected.

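### The spirometer is reported to under-read FEV1/FVC by 2–5 %, but airflow limitation is counted at 0.70 and the LLN with no correction described and no sensitivity analysis for it

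*Protocol article*

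**What the plan says.** All centres used the same portable turbine spirometer. In the Equipment section the protocol article says it performed very well in the laboratory against a reference device, while "displaying a 2–5 % underestimation of the FEV_1_ and the FEV_1_/FVC". It adds that "only 2 % of the observed variation in the measurement results could be explained by the type of device used under real-life conditions". In its view the device's small error matters less than factors such as when the test is done.

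On how readings are used, the section says "Winspiro Pro software (MIR) was used to compare the measured values with those in reference tables". Its definition of airflow limitation follows: "Two cut-offs values were used to define AL: FEV_1_/FVC < 0.7 (fixed cut-off) and FEV_1_/FVC < LLN". It mentions neither a device correction nor an adjusted cut-off.

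The Procedure section adds that "an extra calibration procedure was organized twice during the research using a 3 liter calibration syringe and no significant deviations were detected". The Sensitivity analysis section lists three approaches (post-stratification, reweighting, extreme-case simulation), all directed at non-participation. The Sample size section plans for 8 % COPD prevalence, to within 1 percentage point at 95 % confidence.

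**The concern.** Prevalence of airflow limitation is the area of a distribution's tail below a cut-off. If displayed ratios are uniformly low by a few per cent, people whose ratio lies just above the cut-off are counted as obstructed. The error runs in one direction and does not shrink with sample size.

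A share of variance cannot settle this. A shift common to all readings adds nothing to the variance within a study that uses one device, yet it moves everyone relative to the threshold.

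Objectives 1 and 2 (prevalence, and GOLD versus LLN) are threshold counts. The same ratio also governs entry to the cohort and case or control status. A shift in FEV1 also affects the case criterion of FEV1 below 80 % predicted or below its LLN.

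**Working it through.** **The plan's own figure.** n = Z²P(1−P)/d² = 1.96² × 0.08 × 0.92 / 0.01² = 2827.4, rounded up to 2828, as stated. The 95 % half-widths at the observed counts are:

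- before bronchodilation, 247/2974 = 8.3 %: 1.96 × √(0.0831 × 0.9169 / 2974) = 0.99 point
- in the bronchodilator-tested group, 162/2388 = 6.8 %: 1.96 × √(0.0678 × 0.9322 / 2388) = 1.01 points

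**Inputs from the article.** Bias 2–5 % and the two cut-offs (Equipment); the counts 247, 2974, 162 and 2388 (Results). I read the 162 as post-bronchodilator.

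**Assumptions, not in the article.** The bias b is a constant relative shift that applies to the ratio in field use. Ratios are normal with SD s = 0.05–0.07. For the LLN check, healthy people have mean ratio 0.79 and SD 0.05–0.065.

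**Shift of the fixed cut-off.** If displayed = comparator × (1−b), a displayed 0.70 corresponds to 0.70/0.98 = 0.714 or 0.70/0.95 = 0.737 on the comparator. Equivalently, a comparator ratio of 0.70 displays as 0.686 or 0.665.

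**Fixed cut-off, working back.** Anchor the displayed distribution to the observed count: mean m = 0.70 − z·s, with z = −1.385 for 8.3 % and −1.492 for 6.8 %. The corrected proportion is Φ[(0.70(1−b) − m)/s] = Φ(z − 0.70b/s).

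Example: 8.3 %, b = 0.02, s = 0.05 gives Φ(−1.385 − 0.280) = Φ(−1.665) = 4.8 %.

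| Observed | b = 2 %, s = 0.05 to 0.07 | b = 5 %, s = 0.05 to 0.07 |
|---|---|---|
| 8.3 % (247/2974) | 4.8 to 5.7 % | 1.9 to 3.0 % |
| 6.8 % (162/2388) | 3.8 to 4.5 % | 1.4 to 2.3 % |

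With s = 0.08 the 6.8 % becomes 4.8 % and 2.7 %. So the post-bronchodilator figure is roughly 4–5 % at a 2 % bias and 1.4–2.7 % at 5 %.

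**How sensitive is this to shape?** At b = 2 %, s = 0.10 still lowers 8.3 % to 6.4 %, and a left-skewed distribution with s = 0.08 lowers it to 6.3–6.5 %. These are drops of about 1.8–2.0 points.

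**LLN.** The limit is L = 0.79 − 1.645s. A healthy person is flagged if the comparator ratio is below L/(1−b), so the flagged share is Φ[(L/(1−b) − 0.79)/s].

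- s = 0.05: L = 0.708; b = 2 % gives Φ(−1.356) = 8.8 %; b = 5 % gives Φ(−0.900) = 18.4 %
- s = 0.065: L = 0.683; b = 2 % gives Φ(−1.431) = 7.6 %; b = 5 % gives Φ(−1.092) = 13.7 %

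The nominal 5 % therefore becomes 7.6–8.8 % or 13.7–18.4 %.

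**The 2 % variance share.** If two devices are used equally often, a mean difference of δ total SDs explains R² = δ²/4. R² = 0.02 gives δ = 2√0.02 = 0.28. Under normality that moves an 8 % tail to Φ(−1.405 + 0.283) = 13 %. A 2 % share is thus compatible with a material error at a cut-off.

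**The case against.** Several counter-arguments have force.

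- **Size of the ratio bias.** The 2–5 % is given jointly for FEV1 and the ratio. The article does not say which end belongs to which, whether it is relative, or whether it is a mean shift or a spread across tests. The 5 % results rest on an assumption. This stands.
- **Laboratory versus field.** The figure is agreement with one comparator in a laboratory, and the field bias is not given. The syringe checks found no significant deviation, but they test delivered volume and say little about the ratio in patients. The Quality assessment section also accepts expirations shorter than 6 s, which may lower FVC and raise the ratio. The net bias is therefore unknown, possibly smaller. This stands.
- **Clinical work-up.** Flagged participants are examined by a pulmonologist, repeat spirometry, and receive a consensus diagnosis. That limits the effect on diagnosed COPD but does not correct a spirometric prevalence of airflow limitation.
- **Precision target.** The ±1 point is sampling precision for COPD prevalence, so it is a yardstick here and not a limit on bias.
- **Condensed article.** An analysis plan may contain a device analysis, and 'uncorrected' is inferred from silence. But the article sets out its sensitivity analyses and offers a variance argument that does not bear on the issue. That reasoning is on the page.

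A reader might infer that the article calls the device error negligible. It does not: it discloses the bias and calls the error small. A reader might also infer that prevalence is shown to be inflated far beyond 1 point, or that the true figure is 2–3 %. The documents do not support that, because neither the bias in the field nor the spread of the ratio is reported.

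**Conclusion.** The point holds as a gap in robustness, not as a demonstrated error in prevalence. By the article's own statement the instrument under-reads the quantity that is compared with the cut-offs, and nothing described corrects for this or examines it.

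If the bias is a constant relative shift in the field ratio and the normal model with SD 0.05–0.07 is roughly right, a 2 % bias alone takes about 2.6–3.5 points off the pre-bronchodilator 8.3 % (8.3 − 5.7 and 8.3 − 4.8). That is more than the 1-point sampling margin. The drop at 5 % is larger, but that end is not established for the ratio. The LLN definition is affected in the same direction, so choosing it over the fixed ratio does not avoid the problem.

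**What to change.** Add a pre-specified sensitivity analysis beside those for non-participation:

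1. Recount airflow limitation, before and after bronchodilation, with the displayed ratio divided by (1−b) for b from 0 to 5 %. For the fixed criterion this lowers the displayed cut-off from 0.70 to 0.686 at 2 % and 0.665 at 5 %.
2. Recompute FEV1 and the GLI z-scores in the same way, so that the LLN counts and FEV1 criteria are covered.
3. If the data from the earlier device comparison are available, use a calibration equation from them in place of the fixed range of b.
4. Report the range beside the uncorrected prevalence, noting that the net field bias is unknown.
5. In the Equipment section, qualify the variance argument: a small share of variation does not exclude a systematic shift at a threshold.

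The recount uses stored ratios, so it needs no new measurements and no assumption about the distribution's shape. The calibration equation depends on access to the comparison data. The drawback is that the headline prevalence gains a visible range.

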#### Procedure

The pre- and post-bronchodilator spirometry test measurements were recorded. Reversibility testing using 400 μg of salbutamol or 160 μg of ipratropium bromide (for patients older than 60 years or with comorbid cardiovascular disease) was offered to all participants. The second spirometry test was performed 15 (salbutamol) or 45 min (ipratropium bromide) after the first spirometry test. The Spirobank G turbine-microspirometer does not require calibration and has an internal temperature sensor for automatic BTPS conversion [43]. Routine multiple-speed volume calibration checks are not mandatory with this equipment. Nevertheless an extra calibration procedure was organized twice during the research using a 3 liter calibration syringe and no significant deviations were detected.

#### Quality assessment

The ERS/ATS quality criteria were used to assess the acceptability and repeatability of the results [44]. The ATS/ERS criteria of spirometry quality include the following parameters: FVC minimal duration, 6 s; the FVC “end of test” criteria (or the volume-time curve shows an obvious plateau or the volume time curve shows an obvious plateau or the forced exhalation is of reasonable duration); maximum number of FVC maneuvers, 8; absence of artifacts; and maneuver repeatability. The repeatability criteria are used to determine when more than three acceptable FVC maneuvers are required; these criteria are not suitable for the exclusion of results from reports or for the exclusion of subjects from a study [44]. Acceptable repeatability is achieved when the difference between the largest and the second-largest FVC is ≤ 0.150 L and the difference between the largest and the second-largest FEV_1_ is ≤ 0.150 L. For individuals displaying an FVC of ≤ 1.0 L, both of these values are recorded as 0.100 L [44].

After assessment, all spirometry results were classified according to 4 categories: ATS1, all ATS/ERS criteria, including reproducibility, were satisfied; ATS2, all criteria except for duration of expiration > 6 s were satisfied; ATS3, the test was “usable” for the interpretation of the PEF and FEV_1_, and the spirograms displayed good starts and no cough noted during the 1st second of the maneuver; and ATS4, none of the ATS/ERS criteria were satisfied, and the spirograms were not usable. Spirograms scored as ATS1 or ATS2 were considered to be of acceptable quality.

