#### Sensitivity analysis

Sensitivity Analysis is defined as “ a method to determine the robustness of an assessment by examining the extent to which results are affected by changes in methods, models, values of unmeasured variables or assumptions” with the aim of identifying “results that are most dependent on questionable or unsupported assumptions” [45]. It has also been defined as a series of analyses of a data set to assess whether altering any of the assumptions made leads to different final interpretation and conclusions” [46].

With increasing rates of non-participation in surveys and studies, the inherent uncertainty and potential for bias that accompanies non-response increases. Different adjustment methods have been proposed. The choice of an adjustment method depends on the assumptions that are considered plausible regarding the nature of the non-participation and the type of additional sources of data that are available.

In our study no information about the invited persons that refused to participate to the study is available. We assume that the non-participants are missing at random i.e. that the probability of being missing is not dependent on unobserved data, given the observed data.

However since the issue of a possible participation bias is so essential we decided to perform a sensitivity analysis to assess the robustness of our prevalence figures. The sensitivity analysis will be based on three different approaches: (1) a post-stratification strategy, (2) a reweighting procedure and (3) an extreme case scenario i.e. simulation of the impact on the overall prevalence starting from two hypotheses: 1. All of the non-responders are smokers 2. None of the non-responders are smokers. We will compare the results of these simulations with the original prevalence figures [47].

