## Results

Participants aged 35-70 years from the patient list from each center were selected using a random number generator; initially, 4419 individuals were invited to participate in the study. In total, 3133 individuals agreed to participate and met the inclusion criteria. In addition, 2974 participants demonstrated satisfactory quality on spirometry (after comprehensive quality assessment for reproducibility and acceptability) (Fig. 2). Basic spirometry analysis revealed 247 participants with obstructions before bronchodilation (FEV_1_/FVC < 0.7). Good-quality bronchodilator tests were obtained from 2388 participants. Of these participants, 162 were patients with AL (FEV_1_/FVC < 0.7), including 130 patients with irreversible lung obstruction (FEV_1_ < 200 ml or 12 % after bronchodilation).

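### The spirometry quality gate applies a repeatability criterion that the same section calls unsuitable for exclusion, and the sensitivity analysis does not extend to participants without a valid bronchodilator test

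*Protocol article*

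**What the plan says.** All places are in the protocol article.

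- **Quality assessment, the principle.** Repeatability serves to decide whether more manoeuvres are needed; beyond that, "these criteria are not suitable for the exclusion of results from reports or for the exclusion of subjects from a study".
- **Quality assessment, the grading.** Repeatability is among the listed quality criteria: "maximum number of FVC maneuvers, 8; absence of artifacts; and maneuver repeatability". The two top grades are "ATS1, all ATS/ERS criteria, including reproducibility, were satisfied; ATS2, all criteria except for duration of expiration > 6 s were satisfied". ATS3 is usable only for PEF and FEV1, and ATS4 is not usable. The gate is then: "Spirograms scored as ATS1 or ATS2 were considered to be of acceptable quality".
- **Results, the gate in use.** From 3133 participants, "2974 participants demonstrated satisfactory quality on spirometry (after comprehensive quality assessment for reproducibility and acceptability". The count of 247 obstructed before bronchodilation follows.
- **Results, bronchodilator test.** "Good-quality bronchodilator tests were obtained from 2388 participants", of whom 162 had FEV1/FVC below 0.7.
- **Sensitivity analysis.** The section starts from non-participation: "In our study no information about the invited persons that refused to participate to the study is available". The missing-at-random assumption is made for non-participants. Post-stratification, reweighting and an extreme-case scenario are then planned because of possible participation bias. The scenario varies only the smoking status of non-responders.

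**The concern.** There are two linked problems.

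First, the section states a rule and then sets a gate that breaks it. ATS2 waives only the six-second duration, so it still requires repeatability. A test with acceptable manoeuvres and a valid FEV1/FVC, but with its two best efforts too far apart, fits neither accepted grade. If failing repeatability is related to lung function, dropping such tests selects the sample on something close to the outcome.

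Second, a larger group of participants has no good-quality bronchodilator test, and the stated sensitivity analysis is not aimed at them. Refusers, about whom nothing is known, are examined. Participants who passed the baseline gate but lack a valid second test are not, although their baseline FEV1/FVC is the most informative variable available for the purpose. Whether a valid second test exists may depend on baseline obstruction, and then a prevalence computed only in those who have one would be distorted.

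**Working it through.** **Inputs.** Sample size calculations: P = 8%, d = 1 point, 95% confidence, n = 2828, with an allowance for 20% refusal only. Results: 3133 participants, 2974 with satisfactory spirometry, 247 obstructed before bronchodilation, 2388 good-quality bronchodilator tests, 162 with airflow limitation among them.

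**1. The plan's own figure.** n = Z²P(1−P)/d² = 1.96² × 0.08 × 0.92 / 0.01² = 2827.4, rounded up to 2828. It reproduces.

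**2. Flow** (taking the 2388 as a subset of the 2974).
- Lost at the quality gate: 3133 − 2974 = 159, or 5.1%. Retained: 2974/3133 = 94.9%.
- Lost between the gate and a good-quality bronchodilator test: 2974 − 2388 = 586, or 586/2974 = 19.7%.
- Retained for a post-bronchodilator result: 2388/3133 = 76.2%.

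**3. Precision.** Half-width = 1.96 × √(P(1−P)/n).
- At 8% and n = 2974: 0.98 points.
- At 8% and n = 2388: 1.09 points; 2828 − 2388 = 440 below the planned number.
- At the crude 6.8% and n = 2388: 1.01 points.

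**4. Crude prevalence, fixed ratio.** Before bronchodilation 247/2974 = 8.3%. Among those with a good-quality bronchodilator test 162/2388 = 6.8%.

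**5. What the 159 could do to the baseline figure** (assumed risks). Suppose all 159 could be recovered, which is the extreme.
- Twice the observed risk: (247 + 159 × 2 × 0.083)/3133 = 8.7%.
- Three times: (247 + 159 × 3 × 0.083)/3133 = 9.1%.

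The shift from 8.3% is 0.4 to 0.8 points at most under these assumptions, and smaller if fewer than 159 are recoverable.

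**6. What the missing second tests could do** (assumed). Suppose the 162 are post-bronchodilator values and all come from the 247 baseline positives. The other 247 − 162 = 85 either tested negative or had no valid second test.
- None of the 85 is a case: 162/2974 = 5.4%.
- All 85 are untested cases: 247/2974 = 8.3%.

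In between, let q be the share of the 247 with a valid second test, and assume those tested are representative of the 247. Prevalence is then [162/(247q)] × 247/2974 = 162/(2974q):

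| q | Prevalence |
|---|---|
| 1.0 | 5.45% |
| 0.9 | 6.05% |
| 0.803 (same completeness as overall, 2388/2974) | 6.78% |
| 0.7 | 7.78% |

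The crude 6.8% is right only if testing was equally complete in obstructed and unobstructed people. The article does not give q.

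**The case against.** The strongest replies, and what stands of each:

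- **The loss to repeatability is unquantified.** Correct. The 159 include tests graded ATS3, usable only for PEF and FEV1, and ATS4, not usable; neither yields a ratio under any repeatability rule. A reader might infer that 159 people were dropped for non-repeatability. The documents support only a number between 0 and 159, and because the flow diagram is not shown, exclusion is inferred from the gate and the reported counts.
- **The 2388 is never declared the prevalence denominator.** Also correct. The definition of airflow limitation under Equipment is not confined to post-bronchodilator values, and the baseline figure rests on 2974, above the planned 2828. A reader might infer that prevalence as a whole rests on 76% of participants; that holds only for a post-bronchodilator figure on 2388.
- **People without a second test are not without a diagnosis.** In Study III, anyone newly found obstructed before or after the reversibility test is examined by a pulmonologist, has spirometry at T1 within six months, and a consensus diagnosis is planned. It would be wrong to conclude that all 745 (159 + 586) lack an evaluable COPD status. How these later results enter prevalence is not stated.
- **Post-stratification and reweighting may help.** They would correct part of the loss if applied to the analysed set. As written, they serve non-participation.
- **Missing-data handling is often left to a fuller document.** True, and silence alone would be no finding. Here, however, the article does fix a sensitivity analysis and gives its scope, and the repeatability contradiction is in the text itself.
- **A precision loss of 0.09 points is small.** Agreed; precision is a minor part of this point.

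**Conclusion.** The contradiction within Quality assessment stands, and the Results show the gate in use. Its effect on numbers is between 0 and 159 participants, at most 5.1%.

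The second part stands in limited form. A post-bronchodilator prevalence computed on 2388 is a complete-case figure in 76.2% of participants, with a half-width of 1.09 points at 8% against the planned 1 point, and the stated sensitivity analysis does not extend to those left out. Under the assumptions in step 6, prevalence among the 2974 lies between 5.4% and 8.3%. That is from about 1.3 points below to 1.5 points above the crude 6.8%, so it can exceed the planned precision.

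This rests on three readings that the article does not settle: the 162 are post-bronchodilator values, the 2388 lie within the 2974, and no baseline-negative person becomes a case. A reader might infer that prevalence is biased downward because obstructed people repeat less well. The documents give no data on that, and for the missing second tests the error can go either way.

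**What to change.** 1. Reconcile the ATS grading with the repeatability sentence. In the main prevalence analysis, keep acceptable but non-repeatable tests that give a valid FEV1/FVC. Leave out ATS3 tests usable only for PEF and FEV1, and ATS4 tests. Repeat the analysis in ATS1/ATS2 only, and report how many tests failed on repeatability alone.
2. State the denominator for each prevalence (before and after bronchodilation, fixed ratio and LLN), and say whether the 162 are post-bronchodilator values.
3. Extend the sensitivity analysis to participants without a valid post-bronchodilator test. Standardise or impute on baseline FEV1/FVC, age, sex, smoking and centre, and use the pulmonologist and T1 results for those obstructed at baseline. Show the figure on 2388 alongside. Report the number of the 247 with a valid second test, since that count shows most directly whether the crude figure is distorted. Covariates may be incomplete for some: Table 1 denominators fall to 3059 and 2912 for some items.

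Cost: re-grading up to 159 stored tests and re-analysing existing data, with no new participants. The downside is that a few noisier tests are retained and one extra model has to be described.
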